## 16. Appendices

### 16.1 Appendix I: Toxicity Scale for laboratory values

| SERUM CHEMISTRY                              |                             |                             |                       |                                              |
|----------------------------------------------|-----------------------------|-----------------------------|-----------------------|----------------------------------------------|
| Lab value                                    | Mild
(Grade 1)           | Moderate
(Grade 2)       | Severe
(Grade 3)   | Potentially Life
Threatening
(Grade 4) |
| Sodium – Hyponatremia
mmol/L              | < LLN - $\geq 132$          | < 132 - $\geq 130$          | < 129 - $\geq 125$    | <125                                         |
| Sodium – Hypernatremia
mmol/L             | $\geq$ ULN - < 150          | $\geq 150$ - < 155          | $\geq 155$ - < 160    | $\geq 160$                                   |
| Potassium – Hyperkalemia
mmol/L           | $\geq$ ULN - < 5.5          | $\geq 5.5$ - < 6.0          | $\geq 6.0$ - < 7.0    | $\geq 7.0$                                   |
| Potassium – Hypokalemia
mmol/L            | < LLN - $\geq 3.5$          | < 3.5 - $\geq 3.4$          | < 3.4 - $\geq 3.2$    | < 3.2                                        |
| Calcium – Hypercalcaemia
mmol/L           | $\geq$ ULN - < 2.9          | $\geq 2.9$ - < 3.1          | $\geq 3.1$ - < 3.4    | $\geq 3.4$                                   |
| Calcium - Hypocalcaemia
mmol/L            | < LLN - $\geq 2.0$          | < 1.75 - $\geq 2.0$         | < 1.6 - $\geq 1.75$   | < 1.5                                        |
| Serum creatinine - mg/dL                     | $\geq$ ULN - < 1.5 x
ULN | $\geq 1.5$ - < 3 x ULN      | $\geq 3 - 6$ x ULN    | > 6 x ULN                                    |
| Alkaline Phosphatase -
increase by factor | > 1.25 - < 2.0 x
ULN     | $\geq 2.0$ - < 3.0 x
ULN | $\geq 3.0$ x ULN      |                                              |
| Liver Function Tests -
increase by factor | > 1.0 - < 2.5 x
ULN      | $\geq 2.5$ - < 4 x ULN      | $\geq 4$ x ULN        |                                              |
| Total Bilirubin - increase by
factor      | > ULN – 1.5 x
ULN        | > 1.5 - 3.0 x ULN           | > 3.0 - 10.0 x
ULN | > 10.0 x ULN                                 |
| Cardiac Troponin I                           | >ULN – <2.0 x
ULN        | $\geq 2.0$ - < 5.0 x
ULN | $\geq 5.0$ x ULN      |                                              |
| Total Cholesterol
mg/dL                   | > ULN - 300                 | > 300 - 400                 | > 400                 |                                              |

| HEMATOLOGY                                                           |                        |                           |                     |                                              |
|----------------------------------------------------------------------|------------------------|---------------------------|---------------------|----------------------------------------------|
| Lab Value                                                            | Mild
(Grade 1)      | Moderate
(Grade 2)     | Severe
(Grade 3) | Potentially Life
Threatening
(Grade 4) |
| Hemoglobin (Female) - g/dl                                           | < LLN - $\geq$ 10.5    | < 10.5 - $\geq$ 10.0      | < 10.0              |                                              |
| Hemoglobin (Male) - g/dl                                             | < LLN - $\geq$ 12.0    | < 12.0 - $\geq$ 11.0      | < 11.0              |                                              |
| WBC Increase - cell/mm                                   | $\geq$ ULN - < 15,000  | $\geq$ 15,000 - < 20,000  | $\geq$ 20,000       |                                              |
| WBC Decrease - cell/mm                                   | < LLN - $\geq$ 2,500   | < 2,500 - $\geq$ 1,500    | < 1,500             |                                              |
| Lymphocytes Decrease - cell/mm                           | < 1,000 - $\geq$ 750   | < 750 - $\geq$ 500        | < 500               |                                              |
| Neutrophils Decrease - cell/mm                           | < 2,000 - $\geq$ 1,500 | < 1,500 - $\geq$ 1,000    | < 1,000             |                                              |
| Platelets Decreased - cell/mm                            | < LLN - $\geq$ 100,000 | < 100,000 - $\geq$ 75,000 | < 75,000            |                                              |
| URINE                                                                |                        |                           |                     |                                              |
| Protein                                                              | Trace - $\leq$ 1+      | > 1+ - $\leq$ 2+          | > 2+ - $\leq$ 3+    | > 3+ - nephritic syndrome                    |
| Glucose                                                              | Trace                  | 1+                        | 2+                  | >2+                                          |
| Blood (microscopic) – red blood cells per high power field (rbc/hpf) | $\geq$ 0- $\leq$ 10    | $\geq$ 10 - < 50          | $\geq$ 50           | Gross                                        |
| Blood (measured by Combur urinsticks)                                | Trace - $\leq$ 1+      | > 1+ - $\leq$ 2+          | > 2+ - $\leq$ 3+    | > 3+                                         |
| SYSTEMIC QUANTITATIVE                                                |                        |                           |                     |                                              |
| Tachycardia - beats per minute                                       | 101 - 115              | 116 – 130                 | $\geq$ 131          |                                              |
| Bradycardia - beats per minute                                       | 54 - 50                | 49 – 45                   | $\leq$ 44           |                                              |
| Hypertension (systolic) - mm Hg                                      | 141 - 155              | 156 – 165                 | $\geq$ 166          |                                              |
| Hypertension (diastolic) - mm Hg                                     | 91 - 95                | 96 – 100                  | $\geq$ 101          |                                              |
| Hypotension (systolic) - mm Hg                                       | 89 - 85                | 84 – 80                   | $\leq$ 79           |                                              |

## 16.2 Appendix II: Case Definitions Acute Myocarditis / Pericarditis

### Case Definition for Acute Myocarditis

A possible case of acute myocarditis is defined by the following criteria and the absence of evidence of any other likely cause of symptoms:

Presence of dyspnea, palpitations, or chest pain of probable cardiac origin in a patient with either one of the following:

- Electrocardiogram (ECG) abnormalities beyond normal variants, not documented previously, including
  - ST-segment or T-wave abnormalities,
  - Paroxysmal or sustained atrial or ventricular arrhythmias,
  - AV nodal conduction delays or intraventricular conduction defects, or
  - Continuous ambulatory electrocardiographic monitoring that detects frequent atrial or ventricular ectopy

Or

- Evidence of focal or diffuse depressed left-ventricular (LV) function of indeterminate age identified by an imaging study (e.g., echocardiography or radionuclide ventriculography).

A probable case of acute myocarditis, in addition to the above symptoms and in the absence of evidence of any other likely cause of symptoms, has one of the following:

- Elevated cardiac enzymes, specifically, abnormal levels of cardiac troponin I, troponin T, or creatine kinase myocardial band (a troponin test is preferred);
- Evidence of focal or diffuse depressed LV function identified by an imaging study (e.g., echocardiography or radionuclide ventriculography) that is documented to be of new onset or of increased degree of severity (in the absence of a previous study, findings of depressed LV function are considered of new onset if, on follow-up studies, these findings resolve, improve, or worsen); or
- Abnormal result of cardiac radionuclide imaging (e.g., cardiac MRI with gadolinium or gallium-67 imaging) indicating myocardial inflammation.

A case of acute myocarditis is confirmed if histopathologic evidence of myocardial inflammation is found at endomyocardial biopsy or autopsy.

### Case Definition for Acute Pericarditis

A possible case of acute pericarditis is defined by the presence of

- Typical chest pain (i.e., pain made worse by lying down and relieved by sitting up and/or leaning forward) and no evidence of any other likely cause of such chest pain.

A probable case of acute pericarditis is a possible case of pericarditis, or a case in a person with pleuritic or other chest pain not characteristic of any other disease, that, in addition, has one or more of the following:

- Pericardial rub, an auscultatory sign with one to three components per beat,
- ECG with diffuse ST-segment elevations or PR depressions without reciprocal ST depressions that are not previously documented, or
- Echocardiogram indicating the presence of an abnormal collection of pericardial fluid (e.g., anterior and posterior pericardial effusion or a large posterior pericardial effusion alone).

A case of acute pericarditis is confirmed if histopathologic evidence of pericardial inflammation is evident from pericardial tissue obtained at surgery or autopsy.

## 16.3 Appendix III: SCORAD Evaluation Form

|                       |                                                                                                          |                               |                                                                                                                                                                                                                                                             |
|-----------------------|----------------------------------------------------------------------------------------------------------|-------------------------------|-------------------------------------------------------------------------------------------------------------------------------------------------------------------------------------------------------------------------------------------------------------|
| POX-MVA-008           |                                                                                                          | SCORAD Evaluation Form |                                                                                                                                                                                                                                                             |
| Visit No.             |                                                                                      | Visit date                    |  |
| Subject Study No.     |      |                               |                                                                                                                                                                                                                                                             |
| Examiner (Name) _____ |                                                                                                          |                               |                                                                                                                                                                                                                                                             |

  

[figure not shown]
[figure not shown]

Figures in parenthesis for children under two years

**A: EXTENT.** Please indicate the area involved \_\_\_\_\_

**B: INTENSITY.** (as rated below) \_\_\_\_\_

| CRITERIA         | INTENSITY |
|------------------|-----------|
| Erythema         |           |
| Edema/Papulation |           |
| Oozing/crust     |           |
| Excoriation      |           |
| Lichenification  |           |
| Dryness          |           |

Is evaluated on individual areas

**C: SUBJECTIVE SYMPTOMS**  
**PRURITUS + SLEEP LOSS**  
\_\_\_\_\_

**SCORAD A/5 + 7B/2 + C**

\_\_\_\_\_

Visual analog scale (average for the last 3 days or nights)

**PRURITUS (0 to 10)**

**SLEEP LOSS (0 to 10)**

0 1 2 3 4 5 6 7 8 9 10

0 1 2 3 4 5 6 7 8 9 10

## 16.4 Appendix IV: Proposed Extension Phase of the POX-MVA-008 trial

### 16.4.1 General Information and Rationale for an Extension Phase of the POX-MVA-008 trial

- The original protocol was designed to evaluate immunogenicity and safety of MVA-BN® (IMVAMUNE®) in vaccinia-naïve subjects with diagnosed atopic dermatitis compared to healthy subjects.

This extension phase implements the following major changes to Bavarian Nordic protocol POX-MVA-008:

- A protocol extension, which allows the recruitment of a further 100 healthy and 200 vaccinia-naïve subjects with diagnosed atopic dermatitis. A visit schedule describing examinations performed is detailed in section 16.4.2 “Extension Protocol Flowchart”.
- An additional interim analysis (proposed in Amendment #2) will no longer be conducted at the end of the main phase of the study (once 260 subjects have been enrolled in the main study and have completed their Visit 5). An analysis of the complete study population will be done once all 560 subjects have been enrolled and have completed their Visit 5, and will be performed as described under section 9.4. Once all 560 subjects have completed their Follow-Up assessment an addendum will be prepared including all follow-up data.
- The enrollment of a total of 300 subjects with diagnosed atopic dermatitis will allow the detection of 1 (one) unexpected adverse reaction in 100 (one hundred) subjects with 95% confidence, provided there is no background incidence of the respective adverse reaction.
- The sample size of 300 subjects with atopic dermatitis will meet the requirements suggested by CBER’s “Current Thinking” position paper regarding the data recommended in support of the use of MVA vaccines in a post-event setting under an EUA for individuals with contraindications to vaccinia vaccines.

The changes are not considered to have any negative influence on the study procedure in general, on the safety of the participants or on the validity of the main study results.

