| Route of administration       | Each immunization consists of one subcutaneous (s.c.) injection in the non-dominant upper arm.                                                                                                                                                                                              |
| Study duration                | Up to 39 weeks for each subject                                                                                                                                                                                                                                                             |
| Sample size                   | The total sample size will be 260 (130 per group).
In an extension phase, 100 additional healthy subjects and 200 additional subjects with diagnosed atopic dermatitis (Group 2) will be enrolled.                                                                                       |
| Study design                  | Open-label, controlled, 2 study groups:
Group 1: Healthy, vaccinia naïve subjects without atopic disease (n = 130)
Group 2: Vaccinia naïve subjects with diagnosed atopic dermatitis (n = 130)                                                                                        |

[figure not shown]

| Visit Days |    |        |         |            |            |              |
|------------|----|--------|---------|------------|------------|--------------|
| -28- -1    | 0  | 7 - 10 | 28 - 35 | V3 + 10-14 | V3 + 28-35 | V3 + 182-210 |
| Scr        | V1 | V2     | V3      | V4         | V5         | F-U          |

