**3.2.4 Protocol Extension**

After enrollment of 130 subjects each in Group 1 and Group 2, the enrollment into the two study groups will be extended by another 100 vaccinia naïve healthy subjects and 200 vaccinia naïve subjects with diagnosed atopic dermatitis. Please refer to Appendices IV and V for details of the protocol extension.

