## **4. Selection of subjects**

### **4.1 Recruitment procedure**

Volunteers will be recruited actively. Methods of recruitment mainly include Investigator databases and referrals from dermatological clinics and general practitioners specialized on dermatology. Recruitment strategies including paid advertisements, announcements and distribution of flyers will be evaluated.

In total, 560 individuals (260 subjects in the main study and then a further 100 healthy and 200 AD subjects in the extension phase) as defined in Section 4.2 will be enrolled. After signing the Informed Consent, subjects undergo screening procedures to check eligibility due to the following inclusion/exclusion criteria. In the event of a screen failure secondary to mild or limited acute illness or abnormal laboratory values the patient may be re-screened after resolution of the event. Re-screening may require only an additional blood draw or a complete re-screening evaluation, depending on the circumstances of and the time interval from the initial screening failure.

The Investigator will keep a log of subjects screened for the study, and provide the reason in case of exclusion.

Information about every patient entering the study will be provided to the contracted CRO.

Enrollment will be tracked to ensure that at least 50% of the subjects enrolled into Group 2 of the trial have active Atopic Dermatitis rather than history of Atopic Dermatitis. If it becomes apparent that less than 50% of group 2 have active AD then further enrollment of subjects with history of AD will be temporarily halted until the balance is once again achieved.

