### 9.3 Study cohorts/data sets to be evaluated

For the statistical analysis the included subjects will be divided up into the following datasets:

Safety set (SAS): This is the subset of subjects who received at least one dose of study vaccine and for whom any safety data are available.

The final safety analysis will be performed on this population.

Full-analysis set (FAS): This is the subset of subjects who had received at least one dose of study vaccine and for whom any data are available.

Modified Full Analysis Set (MFAS):

This set is defined to consist of all enrolled vaccinia-naïve healthy (Group 1) and at least 300 atopic dermatitis (Group 2) subjects.

- who have been enrolled as vaccinia-naïve based on the verbal confirmation of the volunteer not to have had a smallpox vaccination in the past and on examination of both arms for absence of a typical smallpox vaccination scar.
- who had received both doses of study vaccine and completed all study visits including Visit 4 and
- for whom safety data are available.

Per Protocol (PP) set: This is the subset of subjects who adhere to all protocol conditions, however, not relevant protocol violators can be included into this dataset.

The decision whether a protocol deviation is relevant or not for the classification of subjects to subsets should be made case-by case in a blind review meeting.

The primary population dataset for humoral immunogenicity analysis (ELISA and PRNT) will be the PP set. All confirmatory testing is based on this population. For further descriptive purposes, the same statistical procedures will be applied to the FA dataset.

ELISPOT Analysis Set (EAS):

This set is defined as the alternative PPS for the ELISPOT data analysis. It consists of all subjects with

- a complete ELISPOT data set (Visits 1, 2 and 4 available)
- the administration of both study vaccinations
- without any relevant major protocol violations for this data set.

ELISPOT data analysis will be descriptive and performed on both the EAS and the FAS.

Since two different vaccine lots will be used during the conduct of the study, a stratified subgroup analysis comparing subjects vaccinated either with vaccine lot 0170505 or vaccine lot 0040707 will be performed.

Any subject not included in the Full Analysis Set (FAS) will be considered a drop-out.

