| Telephone Follow-up for SAEs, SIAEs and AEs that were still ongoing at visit 5                  |           |         |         |         |                  |                       | X                  |
| Review baseline signs and symptoms                                                              | X         | X       |         |         |                  |                       |                    |
| Approx. blood sampling in ml                                                        | 14        | 16      | 30      | 16      | 30               | 16 (+14)  | (14)   |

 If clinically indicated additional visits may be necessary between scheduled visits and possibly additional blood draws may occur. Visits occurring between indicated scheduled visits will be identified with letters to indicate sequence of the visit until the next scheduled visit occurs (e.g. 1A, 1B etc. will indicate extra visits between visit 1 and 2).

 Consent process must be completed and form signed before any study-related procedures are conducted.

 Serum or urine pregnancy test, women of childbearing potential only. At screening visit, a serum test must be performed.

 Only required if clinically indicated.

 The Diary Card should be completed daily for 7 days. If symptoms persist at day 7, temperature/symptom measurements should be recorded each day until resolved.

 Approximate amount of blood needed for analysis: Safety lab: app.14 ml, Antibody analysis: app. 16 ml.

Amount of blood taken during the extension phase: app. 150 ml

 Group 2 (AD) only

For clarification:

Lot 170505: 1st enrolment period is from subject 1 to subject 177 (main phase)

Lot exchange: 2nd enrolment period is from subject 178 to subject 260 (main phase)

Lot exchange: 3rd enrolment period is from subject 261 to subject 530 (extension study)

RESTRICTED BUSINESS PROPRIETY

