### 16.4.4 Statistical Considerations

The primary objective of this protocol extension is to estimate the frequency of common and uncommon reactions in 300 vaccinia-naïve subjects with diagnosed atopic dermatitis. This sample size will allow the detection of 1 (one) unexpected adverse reaction in 100 (one hundred) subjects with 95% confidence, provided there is no background incidence of the respective adverse reaction.

The below table provides information on different scenarios for this assumption. The following sample sizes are needed to detect 1, 2 or 3 ADR with 95% certainty:

| Expected incidence of ADR | Number of subjects required to detect 1 ADR | Number of subjects required to detect 2 ADR | Number of subjects required to detect 3 ADR |
|----------------------------------|---------------------------------------------|---------------------------------------------|---------------------------------------------|
| 1:10                             | 28                                          | 46                                          | 61                                          |
| 1:50                             | 148                                         | 235                                         | 313                                         |
| 1:100                            | 298                                         | 473                                         | 627                                         |

---

 Calculated by solving the following equation for  $N$ :  $B(p_a; N, N_A - 1) = \beta$ , where  $B$  is the accumulated binomial distribution,  $N_A$  is the number of adverse events we wish to (be able to) detect and  $\beta = 0.05$ .

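### The extension's enrolment figures conflict (530 versus 560 overall, 300 versus 330 with atopic dermatitis), and five of the nine detection-table entries fall one subject short of 95%

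*Protocol*

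**What the plan says.** The main phase is fixed in the synopsis: "The total sample size will be 260 (130 per group" group). Section 3.2.4 then adds "another 100 vaccinia naïve healthy subjects and 200 vaccinia naïve subjects with diagnosed atopic dermatitis". Section 4.1 gives the sum: "In total, 560 individuals (260 subjects in the main study and then a further 100 healthy and 200 AD subjects in the extension phase"). The lot table in Section 16.5 (Appendix V) agrees, with 230 healthy and 330 AD subjects, 560 in all, of whom 383 are planned for the second vaccine lot. Section 16.4.1 adds that the complete study population is analysed once all 560 have been enrolled and have completed Visit 5.

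Three places use other numbers:

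- Section 16.4.1 bases the extension on an AD total of 300: "The enrollment of a total of 300 subjects with diagnosed atopic dermatitis will allow the detection of 1 (one) unexpected adverse reaction" in 100 subjects with 95% confidence.
- Section 16.4.4 sets the primary objective of the extension, which is to "estimate the frequency of common and uncommon reactions in 300 vaccinia-naïve subjects with diagnosed atopic dermatitis".
- The clarification under the flow chart in Section 16.4.2 reads "Lot exchange: 3rd enrolment period is from subject 261 to subject 530 (extension study").

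Section 9.3 defines the modified full analysis set (MFAS), which Section 9.4 uses for the emergency-use safety package. It is to contain "at least 300 atopic dermatitis (Group 2) subjects" who received both doses, completed the visits through Visit 4 and have safety data.

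Section 16.4.4 introduces its table of detection sizes with "The following sample sizes are needed to detect 1, 2 or 3 ADR with 95% certainty". A footnote gives the formula: the cumulative binomial probability set equal to 0.05 and solved for N.

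**The concern.** The enrolment target is stated in two ways that differ by 30 subjects. A site or monitor who follows the note in Section 16.4.2 would close enrolment at subject 530. One who follows Sections 3.2.4, 4.1 or 16.5 would continue to 560. Closing at 530 would leave the trigger for the complete analysis in Section 16.4.1 unmet, and the second-lot cohort 30 below the number in Section 16.5.

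The AD total has the same gap. Where 300 is called the enrolled total, it coincides with the minimum number of completers that the MFAS requires, and no allowance for loss remains.

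The detection table is a smaller matter. It presents its entries as sizes needed for 95% certainty, so each entry should reach 95% under the footnote's formula.

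**Working it through.** **Enrolment counts.** Inputs: 130 per group (synopsis); +100 healthy and +200 AD (Sections 3.2.4, 4.1); lot table (Section 16.5); enrolment periods 1–177, 178–260 and 261–530 (Section 16.4.2).

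- AD by increments: 130 + 200 = 330. AD by lot table: 72 + 258 = 330.
- Healthy by increments: 130 + 100 = 230. By lot table: 105 + 125 = 230.
- Overall: 230 + 330 = 560, and 177 + 383 = 560.
- Main phase by enrolment periods: 177 + 83 = 260, which agrees with the synopsis.
- Extension by the enrolment note: 530 − 260 = 270, against 100 + 200 = 300.
- Second lot by the enrolment note: 530 − 177 = 353, against 383.

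The gap is 30 and lies wholly in the third enrolment period. The protocol does not split the 530 by group. With 230 healthy subjects, 530 − 230 = 300 are AD, which matches the total in Section 16.4.1. At the other extreme, with all 330 AD subjects enrolled, only 530 − 330 = 200 healthy subjects remain, 30 below the planned 230.

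**Detection claim.** The probability of seeing at least one reaction of incidence 0.01 among n subjects is 1 − 0.99^n:

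- n = 300: 1 − 0.99^300 = 0.9510. The claim in Section 16.4.1 is reproduced.
- n = 330: 1 − 0.99^330 = 0.9637.

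**Room for loss against the MFAS.** With 330 enrolled, 330 − 300 = 30 subjects (9.1%) may fail to qualify. With 300 enrolled, none may.

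**Detection table.** For r reactions at incidence p, P(X ≥ r) = 1 − B(p; N, r − 1), where B is the cumulative binomial. The continuous root is the N that solves B = 0.05 exactly; for r = 1 and p = 0.01 it is ln 0.05 / ln 0.99 = 298.07.

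| Incidence | r | Printed N | P(X ≥ r) at printed N | Continuous root | Smallest N with P ≥ 0.95 |
|---|---|---|---|---|---|
| 1:10 | 1 | 28 | 0.94767 | 28.43 | 29 |
| 1:10 | 2 | 46 | 0.95200 | 45.53 | 46 |
| 1:10 | 3 | 61 | 0.95088 | 60.77 | 61 |
| 1:50 | 1 | 148 | 0.94971 | 148.28 | 149 |
| 1:50 | 2 | 235 | 0.94974 | 235.32 | 236 |
| 1:50 | 3 | 313 | 0.95027 | 312.63 | 313 |
| 1:100 | 1 | 298 | 0.94996 | 298.07 | 299 |
| 1:100 | 2 | 473 | 0.95020 | 472.51 | 473 |
| 1:100 | 3 | 627 | 0.94984 | 627.43 | 628 |

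All nine printed entries are the roots rounded to the nearest integer. Four went up and meet 95%. Five went down and miss it, each by one subject. The largest shortfall is 0.95 − 0.94767 = 0.0023, or 0.23 percentage points.

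**The case against.** The strongest reply is that nothing of substance fails. The sentence in Section 16.4.1 is arithmetically true. The operative recruitment sections consistently give 330 AD subjects, and 300 can be read as the minimum needed with 330 enrolled to secure it. The table entries follow the footnote's equation to the nearest integer, and no design decision uses 28, 148, 235, 298 or 627.

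Much of this stands. A reader might infer from the conflict that the extension is undersized or that the MFAS minimum cannot be reached. The documents do not support that: it would follow only if 300 AD subjects were enrolled, and the recruitment sections enrol 330. A reader might also apply the synopsis's drop-out allowance of about 5% to the 300. That allowance belongs to the immunogenicity sample size. The safety set in Section 9.3 needs only one dose and any safety data, and under Section 5.5 subjects who leave before the first vaccination are replaced. Nor is the 300 in the Initially Planned column of Section 16.5 a contradiction; it is labelled as history beside the new total.

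Two things do not stand. Section 16.4.1 calls 300 the enrolled total, not a minimum. And reading 300 as a minimum does not explain why enrolment ends at subject 530. For the table, rounding to nearest is not enough when the entry is offered as the size needed.

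**Conclusion.** The concern holds as a contradiction in the current text. Enrolment ends at 530 in one place and at 560 everywhere else that an overall total is given, and the AD total is 300 in Sections 16.4.1 and 16.4.4 against 330 by the protocol's own increments and lot table. Each gap is 30 subjects. At the operative 330, the probability of detecting a 1-in-100 reaction is 96.4%, so neither the size of the extension nor its 95% claim is at fault. The consequence is conditional: if enrolment stopped at 530 and 230 of those were healthy (an assumption, since the protocol gives no split), the MFAS minimum would require every enrolled AD subject to qualify. The analysis trigger of 560 would be missed under any split. The table error is minor: five entries, one subject each, at most 0.23 percentage points, from rounding and not from a wrong formula.

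**What to change.** 1. In Section 16.4.2, correct the third enrolment period to subjects 261 to 560. This takes 560 as intended, as the other sections do. If 530 is intended, Sections 3.2.4, 4.1, 16.4.1 and 16.5 and the synopsis must change instead.
2. In Sections 16.4.1 and 16.4.4, state that 330 AD subjects are enrolled so that at least 300 are evaluable, matching the MFAS in Section 9.3. Give the detection probability for a 1-in-100 reaction as 95.1% at 300 and 96.4% at 330. A separate threshold of 299 is not needed and would compete with the MFAS minimum.
3. In the table of Section 16.4.4, raise 28, 148, 235, 298 and 627 to 29, 149, 236, 299 and 628.

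The cost is a correction of figures and wording in Appendix IV. It needs no patients beyond the 560 already stated and no change to the analysis.
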